#### Assessment (NAT counsellors)

Prior to the start of the intervention, the NAT counsellors will complete a demographic questionnaire, collecting information such as age, gender and years of formal education. To gain deeper insights into the counsellors’ motivations, experiences and expectations, we will conduct focus group discussions with all groups of counsellors. These qualitative data will provide a valuable context for understanding the counsellors’ perspectives and potential challenges they may face. Additionally, counsellors will rate their experience as active NAT counsellors by means of a standardized questionnaires (positive experiences and problems/difficulties and four questions about evaluation of having been adequately prepared, usefulness of supervision and their motivation to continue). After each NAT session, each NAT counsellor completes a one-page NAT-adherence protocol for each client.

### Plans to promote participant retention and complete follow-up

NAT counsellors will organise face-to-face follow-up sessions to ensure a personalised and supportive environment for participants. To increase engagement with the online assessment, public health experts and research assistants will be on site to support clients. In the event of a participant dropping out or deviating from the intervention, efforts will be made to collect relevant outcome data, allowing for a comprehensive analysis of the factors influencing participation outcomes, while respecting the participants’ right to withdraw from the study. In addition, participants will receive vouchers or cash as a monetary incentive (5€) for completing the online surveys, providing a motivational incentive for continued participation and completion of follow-up assessments. These retention strategies are designed to ensure data integrity and maximise the depth of insight gained from the study.

### Data management

All data will be collected with tablets using the software Qualtrics, after informed consent has been obtained from participants. We will adhere to data minimisation principles and collect only necessary information. Voice recorders will be used only for focus groups discussions with the counsellors. Once collected and upon connection with the internet, the data is uploaded to a secure cloud provided by Qualtrics. Qualtrics adheres to high security standards and all response data stored in the EU data centre will be encrypted using the industry standard AES-256/TLS protocol. Data transfer from Qualtrics to the University of Konstanz cloud (Nextcloud) will be secure. Downloaded datasets will be encrypted using Cryptomator prior to their storage. Access to the data will be strictly limited to authorised members of the research team, managed through role-based access controls. Data in the Qualtrics cloud will be deleted by the data manager (technical contact person) one year after the end of the data collection. The coding list will be deleted 10 years after implementation. Research data and back-up copies in the university cloud will be deleted after ten years, with master key files deleted one year after the end of the project. We will use pseudonymisation techniques to protect participants’ identities. Data quality will be ensured through regular checks, including checks for missing values, duplicates and plausibility of data ranges, according to a detailed data management protocol. We have conducted a privacy impact assessment in accordance with Art. 35 Datenschutz-Grundverordnung (DSGVO). We have established a data breach notification procedure to promptly address any potential data incidents.

### Confidentiality

All team members are informed and asked to sign a written commitment to high standards of confidentiality. This written commitment ensures that everyone involved in the study understands their responsibility to protect the privacy of participants. Clinical supervisors will be available to NAT counsellors to discuss client details, to ensure that sensitive information is handled appropriately, and that NAT counsellors have professional support when dealing with difficult cases. Senior implementation staff are responsible for regularly updating master key files and the coding list, ensuring that these files are encrypted and password protected. This centralised responsibility helps to ensure consistent and secure management of sensitive information. Physical records related to the trial are securely stored in a locked cabinet in a restricted access office. This additional layer of security for paper records complements the digital security measures described in the Data Management section. These strict confidentiality measures are designed to protect the privacy and rights of all participants and reinforce our commitment to ethical research practices beyond technical data protection measures.

### Plans for collection, laboratory evaluation and storage of biological specimens for genetic or molecular analysis in this trial/future use

Not applicable.

## Statistical methods

### Statistical methods for primary and secondary outcomes

#### Feasibility assessment

[1a-d] Descriptive statistics (frequencies, percentages, means, standard deviations) will be used to assess the feasibility of NAT and the NAT counselling intervention programme in general (Table 4). These quantitative measures will be complemented by qualitative data from focus groups conducted with NAT counsellors as participants. The focus groups will explore perspectives on the need for the programme, areas for improvement, perceived effectiveness, barriers and facilitators to implementation, participants’ experiences and suggestions for improvement (Table 4). Content thematic analysis will be used to analyse the qualitative data to provide a comprehensive understanding of the feasibility and potential for improvement of the programme, using Nvivo software for data analysis.

**Table 4 Tab4:** Summarises the research questions and associated specific hypotheses

Research question	Alternative hypothesis	Null hypothesis	Ref.
Is the overall programme **sustainable**?	The majority ( > 50%) of refugees who leave the temporary accommodation have taken part in the project.	The minority ( < 50%) of refugees who leave the temporary accommodation have taken part in the project.	1a
	The programme is evaluated positively by stakeholders (refugees, counsellors, social workers).	The programme is evaluated negatively by stakeholders (refugees, counsellors, social workers) regarding issues that cannot be improved.	1b
	Recommendation to indicated treatment is followed by more than 50% of refugees.	Recommendation to indicated treatment is not followed by more than 50% of refugees.	1c
	The majority ( > 50%) of trained counsellor perform the screening and provide the intervention.	Only a minority ( < 50%) of trained counsellors perform the screening and provide the intervention.	1d
Is NAT **effective** (prevention)?	The number of participants with subclinical symptom levels at baseline who require specialised psychotherapeutic treatment after 6–9 months is lower in participants who received NAT than in the control group.	The number of participants with subclinical symptom levels at baseline who require specialised psychotherapeutic treatment after 6–9 months is equal in participants who receive the adapted NET compared to the control group.	2a
	The number of participants with subclinical symptom levels at baseline who do not require treatment after 6–9 months is higher in participants who received NAT than in the control group.	The number of participants with subclinical symptom levels at baseline who do not require treatment after 6–9 months is equal in participants who receive the adapted NET compared to the control group.	2b
Is NAT **effective** (symptom reduction)?	Symptom reduction in participants with subclinical symptom levels is stronger in participants receiving NAT than in the control group (see Table 1).	Symptom reduction in participants with subclinical symptom levels is the same in participants receiving NAT compared to the control group (see Table 1).	3
[4] Is the programme generally cost-**effective**?	The financial costs of the NAT counselling intervention are lower than those of other interventions.	The financial cost of the NAT counselling intervention is equal to or higher than other interventions.	4

[2a+b] Chi-squared tests will be used to compare the frequency of participants with subclinical symptom levels requiring more/less intensive treatment during the programme. Logistic regression analysis will be considered to estimate the odds of refugees with or without NAT requiring more/less intensive treatment (Table 4).

[3] To assess the effectiveness of NAT compared to the comparison groups (see Tables 1 and 4), we will combine the figures resulting from RDD with traditional approaches (GLM, clinical significance). In the RDD, we will calculate a local average treatment effect (LATE) of the intervention on primary (RHS-15) and secondary (LSNS, BRS, SWLS, SSS8) outcomes (see Table 1). To this end, we will firstly test whether the main criteria for a valid RDD are held. Using a graphical method (scatterplot), we will examine the relationship between the eligibility (RHS at baseline) and outcome (follow-up) variables. We expect the RHS score to be discontinuous at the cutoff values. In contrast, we do not expect to see discontinuities in relevant covariates at the cutoff, which would violate the assumptions of an RDD. Next, separate regression lines will be fit on both sides of a cutoff value using an ordinary least squares (OLS) regression as the starting point. Alternative functional forms will be tested with the goal of ensuring an unbiased estimation. The LATE will be computed directly as the difference between the regression lines at the cut-off (intercept). To test the statistical significance of the difference between the two conditions, we will use a *t*-statistic, dividing the treatment effect (difference between regression lines at cut-off) by the sum of the square of the standard errors of the comparison group (*SE*_*comparison*_) and the intervention group (*SE*_*interventio*n_). The calculated *t*-statistic will then be compared to a critical value from the *t*-distribution for the given degrees of freedom (*DF*). The degrees of freedom will be determined based on the number of the observations and the parameters estimated in the two separate regressions. In the most simple form, *DF = n*_*comparison*_
*+ n*_*intervention*_
*- 4*. The test will be two-sided. Moreover, we will run falsification tests and sensitivity analysis to ascertain the validity of the RDD [178], examine whether results are sensitive to the choice of bandwidth [144], run placebo tests on exogenous covariates and on the outcome at values other than the actual cutoffs [145]. Prespecified subgroup analyses will explore potential heterogeneity in treatment effects across different demographic and clinical characteristics. Adjusted analyses will account for potential confounding factors identified a priori.

Generalised linear mixed models (GLMM) with subgroups defined by the RDD will be used in addition and allow for integration of multiple follow-ups, if robust (*N*_min_ is sufficient to detect a small to moderate effect). Thus, to test the efficacy of NAT in comparison to our controls in regards to primary and secondary outcomes, we plan to use separate generalised linear mixed models (GLMMs) in R. To account for non-independence of measurements, we will include individuals as a random part of the models. To account for repeated measures, we will control the within-group variance for the effect of time, i.e. baseline and 3 and 6-month follow-ups, according to A Field, Z Field and J Miles [179]. To estimate the significance of the fixed terms, we plan to fit the models using maximum likelihood (ML), and compare models with and without each fixed term using likelihood-ratio tests [180]. In cases where the interaction term is significant, we will use post hoc Tukey tests using the R package emmeans [181] to assess which contrasts differ significantly. To correct for multiple comparisons controlling the false discovery rate, we will further adjust P-values accordingly [182].

Additionally, effect sizes will be estimated by calculating Cohen’s d [183] for within and between group differences following W Lenhard and A Lenhard [184]. Clinically significant change will be calculated using the reliable change index, following NS Jacobson, LJ Roberts, SB Berns and JB McGlinchey [185].

[4] We will estimate the cost-effectiveness of the NAT counselling intervention programme, respectively (Table 4). To this end, we will use cost-effectiveness analysis (CEA) based on the findings of the described trial and rely on established techniques from development and health economics [186–189]. In the first step, we will calculate the costs the NAT counselling intervention programme (as well as supervision, training, etc). Next, we will take into account prevented costs for specialised treatment, levels of improvement at symptom and daily life functionality (e.g. employment), and disability adjusted life years (DALYs) [190–193]. For each of the two compared strategies, a cost-effectiveness ratio (CER) will be calculated (cost versus outcome) allowing for an incremental cost-effectiveness ratio (ICER) which then allows for comparison of the NAT counselling intervention programme versus TAU and decision of superiority. We hypothesize that the NAT counselling intervention programme presents with a higher cost-effectiveness than TAU.

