### Eligibility criteria

*Refugees.* All adult asylum seekers (≥18 years) living in or arriving at the collaborating initial intake facilities are eligible to participate in the study and are offered NAT step 1, the screening interview with RHS-15 including feedback and referral if needed. Exclusion criteria include: severe cognitive impairment or communication problems that prevent participation in interviews, as well as individuals with severe intellectual or psychiatric disabilities who would qualify for guardianship (legal/ethical considerations).

For NAT steps 2 (checklist intake), 3 (lifeline laying) and 4 (narrative event-telling sessions), participants with an RHS score (items 1–13) between 13 and 36 points (‘yellow group’) are eligible; exclusion and referral to specialist care will occur in the case of acute psychiatric illness, acute suicidal ideation or danger to others, as well as acute and persistent intoxication that would prevent effective NAT sessions.

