### Sample size

Approximately 1’500 refugees reside in the initial intake facilities at the collaborating sites and could potentially participate. We estimate that approximately 30–50% will participate in the study over the years. Figure A.1 shows the power of our study with variations in sample size, effect size and predictors. It is important to note that our sample size will follow the naturalistic parallel group design of our study and thus may differ from the estimated sample size (See Fig. 3).

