### Recruitment

Social workers on site inform refugees in collaborating initial intake facilities and hand out flyers about the programme, including participation instructions. Additionally, NAT counsellors will be present in the facilities on a regular basis. With it, refugees who would like to participate can request to register for participation. Moreover, with bi-monthly visits at the initial intake facilities, public health experts and research assistants will invite refugees to participate in the online self-assessments of the Well-being Monitor.

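### Hypothesis 1a counts everyone who leaves the accommodation although only eligible adults can take part, so the written rate understates uptake and can, but need not, decide whether the 50% benchmark is met

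*Protocol article*

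**What the plan says.** Under the question of whether the programme is sustainable, row 1a of Table 4 has this alternative hypothesis: "The majority ( > 50%) of refugees who leave the temporary accommodation have taken part in the project". The null uses the same denominator: "The minority ( < 50%) of refugees who leave the temporary accommodation have taken part in the project". Neither is limited by age or eligibility. The Feasibility assessment text says that 1a to 1d will be assessed with descriptive statistics, complemented by focus groups with counsellors.

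The Eligibility criteria section defines who can take part: "All adult asylum seekers (≥18 years) living in or arriving at the collaborating initial intake facilities are eligible to participate". It then removes some of these adults: "Exclusion criteria include: severe cognitive impairment or communication problems that prevent participation in interviews", and also people whose severe intellectual or psychiatric disability would qualify them for guardianship.

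The Sample size section gives the only related planning figures: "Approximately 1’500 refugees reside in the initial intake facilities at the collaborating sites and could potentially participate", and "We estimate that approximately 30–50% will participate in the study over the years".

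On the numerator, row 1a does not say which step counts as having taken part. The Eligibility criteria section offers the step 1 screening interview. The Recruitment section adds that on regular visits "public health experts and research assistants will invite refugees to participate in the online self-assessments of the Well-being Monitor".

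**The concern.** A participation rate is meant to show how far the programme reaches the people it is offered to. For that, everyone in the denominator must be able to enter the numerator. Row 1a does not meet this condition as written. Minors and excluded adults who leave a facility are counted as non-participants, although the eligibility rules bar them from taking part. The rate then mixes two things: how many eligible people accept the offer, and what share of departures happens to be ineligible. The second says nothing about sustainability, and it would be expected to differ between sites and over time with the mix of families and single adults.

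Sustainability is the first objective listed in the protocol, and 1a is the first criterion given for it, with a stated cut-off. If the denominator is settled only after the counts are known, that choice could determine how the result is described.

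**Working it through.** **Inputs.** The benchmark is above 50% (Table 4, ref. 1a). The resident pool is about 1,500 and expected participation is 30–50% (Sample size). The ineligible share q is not given anywhere, so a range is assumed.

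**The plan's own figures.** The 50% is a chosen benchmark, so there is no calculation behind it to reproduce. The planning range gives 0.30 × 1,500 = 450 to 0.50 × 1,500 = 750 participants. Exceeding 50% of 1,500 takes at least 751.

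**Formula.** Let r be the uptake among eligible leavers. No ineligible leaver can participate, so the rate as written is r(1 − q). It exceeds 0.5 only if r > 0.5/(1 − q).

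| Assumed q | Uptake r needed among eligible leavers | Written rate if r = 60% |
|---|---|---|
| 0% | above 50% | 60% |
| 5% | above 52.6% | 57% |
| 10% | above 55.6% | 54% |
| 20% | above 62.5% | 48% |
| 30% | above 71.4% | 42% |
| 40% | above 83.3% | 36% |

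At q = 50% or more the benchmark cannot be exceeded at any uptake. At r = 60% the result changes at q = 1 − 0.5/0.6 = 16.7%. The 60% is only an illustration and lies above the 30–50% that the protocol expects.

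**When the denominator matters.** If r is 50% or less, the benchmark is missed under either denominator. If r is above 0.5/(1 − q), it is met under either. The choice decides the result only when r lies between these values: from 50% to 62.5% at q = 20%, for example.

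**Set against the planning range.** There are two readings of the 1,500.

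- If all 1,500 are eligible, as the wording of the Sample size section suggests, then r is 30–50%. Even the upper end does not exceed 50% with q = 0, so the denominator does not decide the result.
- If the 1,500 includes ineligible residents, the same 450–750 participants are a larger share of those who could take part. At q = 20% this is 450/1,200 = 37.5% to 750/1,200 = 62.5%. At q = 30% it is 450/1,050 = 42.9% to 750/1,050 = 71.4%. The written rate stays at 30–50% and misses the benchmark, while the rate among eligible people could exceed it. This takes q among residents to be the same as q among leavers.

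**The case against.** **Refugees may be shorthand for the adult study population.** The Eligibility criteria section places that label directly before its adult definition, and the Sample size section describes the resident refugees as possible participants. The consent section, the section on assessment of refugees and row 1c use the word for people who are already in the study. This reading is possible, but it does not settle row 1a. Row 1a identifies its denominator by departure from the facility, not by participation, and the eligibility rule picks out adults as a subset of the residents. Two analysts could compute different rates from the same records.

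**1a is only descriptive.** This stands. No test, error rate, power or progression decision depends on it, and neither the primary outcome nor any effectiveness comparison is touched. It does still have a stated alternative, null and cut-off, so its result can be misdescribed.

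**Counting rules are commonly left to a fuller document.** That would answer a missing detail. Here a denominator is stated, and it does not match the eligibility rule.

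**Two stronger readings are tempting and not supported.** A reader might infer that ineligible leavers do pull the rate below 50%. The documents give no ineligible share, and at q = 5–10% with 60% uptake the rate stays above 50%. On one reading of the planning range the benchmark is missed whatever the denominator. A reader might also infer that people who complete only the online Well-being Monitor inflate the rate. The Trial design, consent and assessment sections place the Monitor after the face-to-face interview or offer it to people already participating, and the Discussion describes the project's invitation as one to screening. The Recruitment sentence leaves the route open but does not establish it.

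**Conclusion.** The point holds as a mismatch between a stated criterion and the protocol's own eligibility rule. Read literally, 1a reports r(1 − q) in place of r, and it raises the uptake required among eligible leavers from above 50% to above 0.5/(1 − q). That is 55.6%, 62.5% and 71.4% at assumed ineligible shares of 10%, 20% and 30%. The direction is certain whenever q is above zero. The size is not known, because q is not documented. Whether the mismatch changes the conclusion on 1a depends on both r and q, and a missed benchmark would not by itself show that the denominator was the cause. What counts as having taken part, including the position of Monitor-only respondents, is an ambiguity to close and not a demonstrated upward bias. The consequence is confined to a descriptive sustainability indicator.

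**What to change.** Restate both 1a hypotheses on one eligible population and one defined step. The alternative would read: more than 50% of the adult asylum seekers who meet the Eligibility criteria and leave the collaborating facilities have completed the NAT step 1 screening interview. The null would be the complement, 50% or fewer. If the facilities cannot count excluded adults, use all adults leaving as the denominator and say so. Some downward bias from excluded adults would remain, but minors would no longer contribute. Report the number of ineligible leavers, and any people who answered only the Well-being Monitor, next to the rate and outside it. Make the change before participation counts are examined.

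The text change is confined to row 1a of Table 4. The practical cost is that the facilities must supply departures by adult status instead of a single total. Any Monitor-only respondents would no longer count towards the benchmark.

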## Interventions

### Explanation for the choice of comparators

In this naturalistic study, the following potential comparators to NAT (treatment condition) evolve: (1) NAT clients awaiting treatment; (2) clients with clinically relevant symptoms who are either (2a) waiting for psychotherapy or (2b) receiving psychotherapy; (3) clients without symptoms waiting for follow-up; and (4) clients before vs. after NAT (individual trajectories of symptom development, Table 1).

**Table 1 Tab1:** Constellation of comparators

Treatment condition	Control condition	Limitation	Mitigation
[1] NAT	Awaiting NAT (RHS 13–36)	Reduced follow-up time points for those who wait for treatment; unknown N	-
[2] NAT	[2a] PT waiting [2b] PT receiving	Clients might still wait but may have started, or already finished PT; higher symptoms of the control group at baseline	Statistical control for the number of treatment sessions, use of the RDD
[3] NAT	Watchful waiting (RHS < 13)	Lower symptoms of the control group at baseline, low symptom levels generally	Evaluate number of clients who present with improving vs. deteriorating symptoms rather than
[4] After NAT	Before NAT	Within subject comparison; potential confounding factors	-

Note: RHS-15 = 15 item Refugee Health Screener with a sum score indicating symptom severity; PT = Psychotherapeutic sessions provided by a licensed Psychotherapist. Threshold to clinical relevance is suggested for ≥37. Watchful waiting is indicated for clients with ≤12 points

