### Criteria for discontinuing or modifying allocated interventions

In the event of danger to self or others, deterioration of trauma reactions or signs of other (comorbid) psychological symptoms, the client will be re-assigned to the red group and receive psychotherapeutic service or treatment at an acute care facility within the German health system. Thereafter, treatment delivery will follow the principles of the red group in full extent.

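### Hypotheses 2a/2b group yellow-range clients by whether they received NAT, so deteriorations noticed before NAT starts fall in the no-NAT group and tilt the prevention comparison towards NAT

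*Protocol article*

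**What the plan says.** Table 4 of the protocol article states two prevention hypotheses for participants with subclinical symptoms at baseline. In 2a, the number "who require specialised psychotherapeutic treatment after 6–9 months is lower in participants who received NAT than in the control group". In 2b, the number "who do not require treatment after 6–9 months is higher in participants who received NAT than in the control group".

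The [2a+b] paragraph under Statistical methods plans chi-squared tests of the need for more or less intensive treatment over the course of the programme. It adds a possible logistic regression to "estimate the odds of refugees with or without NAT requiring more/less intensive treatment".

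Four other places fix who can be in which group:

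- **Eligibility criteria:** for NAT steps 2 to 4, "participants with an RHS score (items 1–13) between 13 and 36 points (‘yellow group’) are eligible". No yellow client is assigned to a control arm.
- **Table 1, row 1:** clients awaiting NAT are the only comparator with the same baseline range. The stated limitation is "Reduced follow-up time points for those who wait for treatment; unknown N", and the mitigation cell holds only a dash.
- **Criteria for discontinuing or modifying allocated interventions:** on deterioration or danger, "the client will be re-assigned to the red group and receive psychotherapeutic service or treatment at an acute care facility". Care then follows the red pathway throughout.
- **Assessment (refugees):** the follow-up interview is timed from screening (6 to 9 months), not from the start of NAT.

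**The concern.** Having received NAT is known only after the wait for it is over. To be counted under NAT, a yellow client must have stayed out of the red group until the first session. A yellow client whose deterioration is noticed sooner is re-assigned, does not receive NAT, and is counted without it. The time between screening and NAT start is therefore protected time for the NAT group, while the no-NAT group collects the early deteriorations.

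For 2a, such a client adds an event to the control side. For 2b, the same client cannot add to the control group's count of people no longer needing treatment. Both effects point towards NAT.

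At stake is the claim that NAT prevents progression to specialised care. A chi-squared test on these groups could support that claim with no preventive effect at all. Baseline adjustment cannot repair it, because the groups are defined by something that happens after baseline. The regression discontinuity analysis does not reach it either: it is specified for hypothesis 3, and both 2a/2b groups lie inside the 13–36 range.

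**Working it through.** The article gives no event rate, waiting time or power figure for 2a/2b, so there is no stated figure to reproduce. The check asks what the grouping rule yields when NAT has no effect.

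**From the article:** groups by receipt; follow-up 6–9 months from screening (midpoint 7.5 used); 95% confidence level; two-sided testing (stated for the regression discontinuity test, assumed here).

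**Assumed:** 300 yellow clients; share taking up NAT q = 0.70; wait W uniform on 0–4 months; deterioration time T exponential with 7.5-month risk r = 10% or 20%; T independent of W; need counted at any time up to follow-up.

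**Step 1: clients who change group.** Rate λ = −ln(1 − r)/7.5. The probability of reaching the slot without deterioration is S = [1 − exp(−4λ)]/(4λ). The number who would have taken NAT but deteriorate first is 300 × q × (1 − S).

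- r = 10%: λ = 0.01405, S = 0.9724, number = 210 × 0.0276 = 5.8.
- r = 20%: λ = 0.02975, S = 0.9428, number = 210 × 0.0572 = 12.0.

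**Step 2: effect of moving them.** With no selection the NAT group has 210 clients and the other group 90, both with event rate r. If every deterioration during the wait is detected and blocks NAT:

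- r = 10%: NAT (21 − 5.8)/(210 − 5.8) = 15.2/204.2 = 7.4%; control (9 + 5.8)/(90 + 5.8) = 14.8/95.8 = 15.4%.
- r = 20%: NAT (42 − 12)/(210 − 12) = 30/198 = 15.2%; control (18 + 12)/(90 + 12) = 30/102 = 29.4%.

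Moving about 6 or 12 of 300 clients roughly doubles the control rate relative to NAT.

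**Step 3: false rejection in NAT's favour** (simulated Pearson chi-squared, two-sided 5%; nominal 2.5% in this direction). Ranges cover repeat runs.

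| Share detected during wait | r = 10% | r = 20% |
|---|---|---|
| All | 56–58% | 81–84% |
| Half | 20% | 32–33% |
| A quarter | 8–9% | 12–13% |
| None | 3% | 3% |

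**Step 4: other assumptions.**

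- With full detection, over 200–300 clients, 50–85% take-up, maximum wait 2–6 months and 10–20% risk, the rate runs from 8% to 100%.
- If half of all events have resolved by follow-up and are not counted, the base case gives 32–33% (r = 10%) and 48–50% (r = 20%). If all have resolved, the bias disappears.
- With a pure waiting-list control (200 clients, everyone willing, waits 0–12 months), event rates are about 5% vs 17% (r = 10%) and 11% vs 32% (r = 20%), with false rejection of 78–80% and 96–97%.

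**Step 5: after the change.** With a month-3 landmark on the base case, event rates are 6.2% vs 6.2% (r = 10%) and 12.6% vs 12.5% (r = 20%). Total rejection is about 5%.

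**The case against.** A reader might infer that the rule decides 2a by construction: that every deterioration before NAT must count against the control group, and that the answer will be yes whatever NAT does. The documents do not support that.

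- **Detection.** The re-assignment rule stands in a section on modifying allocated interventions and does not say in words that it covers the wait. Between screening and follow-up the article describes a monthly online assessment with separate consent, and no passage makes its score trigger re-assignment. Some deteriorations will go unnoticed and will not block NAT. This stands: detection largely drives the size.
- **When need is counted.** Table 4 refers to need after 6–9 months, which can mean status at that visit. The test paragraph refers to the programme as a whole. Clients re-assigned early may have recovered by follow-up. This stands as an ambiguity. It reduces the bias and removes it only if all have recovered.
- **The control group.** Table 4 does not name it, and the reduced follow-up noted for waiting clients could mean that they contribute control time until NAT starts. That would avoid the problem, but the 2a/2b text groups by receipt and says nothing of the kind. The base-case controls are also mostly clients who did not take up NAT, which is not a Table 1 comparator. The pure waiting-list result shows that the bias does not depend on them.
- **Direction.** NAT clients have supervised counsellor contact, so escalation may be noticed more often among them, which works against NAT. This is possible, is not modelled here, and does not undo the selection before NAT.
- **Standing of 2a/2b.** They are not the primary-outcome analysis, and the Limitations section asks for cautious reading of comparisons. That caution neither identifies nor corrects this bias.

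An analysis plan could define the groups properly. The point remains because the article itself fixes the grouping, the comparator and the test.

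**Conclusion.** The concern holds in a qualified form. Grouping by NAT receipt, combined with re-assignment on deterioration and a waiting-list control, builds immortal-time bias in NAT's favour into 2a and 2b, and nothing in the article corrects it.

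The selection mechanism follows from the text, provided some deteriorations are noticed before NAT and at least some of those clients still count as needing treatment. The size does not follow from the text. It rests on the waits, the deterioration rate, the share detected during the wait and the share still in need at follow-up, none of which is given. Under the assumed base case, false rejection of 2a ranges from slightly above nominal (8–13% with a quarter detected) to the usual outcome (56–84% with full detection). No figure is offered for 2b, which needs a further assumption about remission.

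The hypothesis 3 regression discontinuity analysis is not affected, because it compares by baseline score. Only the NAT versus awaiting-NAT contrast in the mixed models shares the problem. The clinical re-assignment rule is not in question.

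**What to change.** For 2a/2b, replace grouping by receipt with a landmark rule:

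1. At a fixed time after screening (for example month 3), take yellow-range clients not yet re-assigned and classify them as NAT started or not started.
2. Count only need for treatment arising after the landmark, and adjust for baseline RHS and site.
3. Report re-assignments before the landmark separately, for the whole yellow group.
4. State whether 2a counts need at the 6–9 month assessment or at any time up to it.

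A model with NAT start as a time-dependent covariate can serve as a sensitivity analysis. It has a different estimand and is not a substitute. Apply the same landmark to the NAT versus awaiting-NAT contrast in the hypothesis 3 mixed models, and leave the regression discontinuity analysis as it is.

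Dropping re-assigned clients is not a remedy. With 200 clients and waits of 0–12 months, dropping everyone who deteriorated before NAT leaves no control events (0% against 5–11% under NAT) and rejects against NAT in 40–95% of null trials.

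Cost: mainly analysis wording, but the dates of NAT start and re-assignment must be recorded, and the article does not say that they are. Events before the landmark leave the contrast, and clients who start NAT after it count as not started, which dilutes a true effect.
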